
### Safety management and adverse events

Any adverse event (AE), which is any untoward medical occurrence, will be documented by the trial site and periodically reviewed by the trial management team. The serious adverse events (SAEs) will be notified to the sponsor, data monitoring safety committee and other sites by the principal investigators (PI) within a stipulated time period of 48 h.

Any adverse event or reaction which (i) is life or limb-threatening, requires hospitalization or a medical intervention or leads to congenital defect is considered a SAE or serious adverse reaction (SAR).

The following will not be included as AE: (i) medical or surgical procedures during the trial (the condition which led to the procedures is deemed an adverse event), (ii) pre-existing condition which did not worsen during trial period and (iii) other unrelated reason for hospitalization (for example, viral fever or incidental illness).

In the intervention arm, if the participant suffers any fracture or other bodily injury which requires hospital care, then it will be considered a notable event. Any food allergy which leads to a hospital visit or admission should be notified. Overall, the lifestyle advise is considered a low-risk intervention and is very unlikely to give rise to any serious adverse events during the trial period.

The participants who conceive during the trial period will be provided with usual ante-natal care based on local unit protocol. Once the woman conceives, the pre-pregnancy lifestyle intervention advised during the trial will be discontinued and pregnancy-specific advice for diet/physical exercise will be given in both arms.

Early pregnancy complications such as threatened, inevitable, incomplete and complete miscarriage and ectopic pregnancy will be recorded. If they are reported during the trial period, they will be recorded as AE or SAE. However, they will not be considered adverse reaction (AR)/serious adverse reaction (SAR) as the intervention is unlikely to have a causal relationship with the early pregnancy complications. Obstetric complications, namely, pregnancy-induced hypertension, pre-eclampsia and gestational diabetes, will be recorded during the follow-up period. The low birth weight and pre-term birth also will be recorded. Since these outcomes will be observed after the intervention period, they will not be recorded as adverse events.

Medical procedures/surgical procedures performed to manage pregnancy complications will be recorded as well. They will not be recorded as AE, but the reason for the medical/surgical procedure will be recorded as AE. The trial site staff will inform the PI/Co-PI within 48 h of recording the SAE and enter the same in the database. If the event requires activation of referral or further hospital care, the process should be facilitated. For other AEs, the trial staff should enter the event in the database within 7 days of recording the event.

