### Blinding

The nature of the intervention will preclude blinding of the participant and the caregiver. However, the primary and most of the secondary outcomes are objective in nature and are less likely to introduce detection bias. However, performance bias cannot be ruled out.

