### Dispensing and scheduling of the individualized lifestyle intervention

#### Weeks 0 and 1 (session 1) (for intervention and control arm)

Post-randomization, same day: blood tests (hormonal and metabolic parameters) and anthropometric measurements, including body weight, will be measured. The blood tests will include blood count, serum follicle stimulation hormone (FSH), serum luteinizing hormone (LH), prolactin, thyroid-stimulating hormone (TSH), dehydroepiandrosterone sulphate (DHEAS), 17 hydroxy progesterone, serum testosterone, sex hormone-binding globulin (SHBG), serum insulin, oral glucose tolerance test with 75 g glucose at 0 and 2 h, fasting lipid profile, HbA1c, uric acid and serum adiponectin. The hormonal and other metabolic parameters will be collected at individual sites and sent to a designated central laboratory for analysis. This central accredited laboratory facility will ensure standardization.

A transvaginal ultrasound will be performed and antral follicle counts and ovarian volume (using TVS with a 6.5 to 8.0 MHz probe). The trial staff will then take the anthropometric measurements while the clinician will obtain the ultrasound report. The clinician will also record information on menstrual regularity and pregnancy status. A pregnancy test will be performed if clinically indicated. The trial staff or nurse will record the quality-of-life score using the prespecified tool [22].

In-person introduction of the programme and the need for weight loss. Participants will be given the food and activity questionnaire and reviewed the same day/week over the phone/in person (flexible). Based on the questionnaire, the dietician and physiotherapist will advise individualized diet/exercise for the intervention arm. For the control arm, one-time advise on diet and exercise will be given (Fig. 1).

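### Hospital-treated injuries are flagged in the intervention arm only, and excluding unrelated hospitalisations contradicts the section's own definitions of adverse and serious adverse events

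*Protocol article*

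**What the plan says.** All of the rules stand in the protocol article under Safety management and adverse events, unless another section is named.

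- General definition: "Any adverse event (AE), which is any untoward medical occurrence, will be documented by the trial site". No arm is named.
- Seriousness: an adverse event or reaction that "is life or limb-threatening, requires hospitalization or a medical intervention or leads to congenital defect is considered a SAE". No arm is named.
- The third listed exclusion from adverse events: "other unrelated reason for hospitalization (for example, viral fever or incidental illness". No arm is named.
- Injury rule: "In the intervention arm, if the participant suffers any fracture or other bodily injury which requires hospital care", it becomes a notable event. No control-arm rule follows.
- Food-allergy rule: "Any food allergy which leads to a hospital visit or admission should be notified". This sentence names no arm, although it comes directly after the intervention-arm sentence.
- Control treatment (Weeks 0 and 1, session 1): "For the control arm, one-time advise on diet and exercise will be given".
- Blinding: "The nature of the intervention will preclude blinding of the participant and the caregiver". The section on sequence generation and allocation concealment adds that the clinical team and the trial staff are told the allocation.

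**The concern.** Adverse-event counts can be compared between arms only if the same event is defined and recorded in the same way in both, with causality judged after recording. Here a named category of harm exists in one arm only, and a separate rule drops some hospitalisations on grounds of relatedness before they reach the safety data.

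Two things are at stake. Injury flags could be read as evidence of harm from the individualised programme when the control arm has no such category. Hospitalisations that meet the section's own criteria for seriousness could also be missing from the data that the monitoring committee reviews. Under Data monitoring, that committee is to report whether one arm is doing poorly against the other, and to review safety.

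**Working it through.** The plan states no injury or hospitalisation rate, so it has no figure of its own to reproduce. The check is mainly of the text. Four events are run through the stated rules:

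| Event | General AE definition | SAE criteria | Third exclusion | Notable event |
|---|---|---|---|---|
| Fracture with admission, intervention arm | met | met | only if classed as unrelated | yes |
| Fracture with admission, control arm | met | met | only if classed as unrelated | no |
| Injury treated at hospital without admission, control arm | met | met if it needs medical intervention | does not apply (concerns hospitalisation) | no |
| Admission for viral fever, either arm | met | met | applies (a named example) | no |

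**Rows 1 and 2.** The same event differs only in the last column. The control count of notable events is zero whatever the true injury rate.

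**Rows 2 and 3.** Control-arm injuries are still adverse events under the general definition. They are lost only if an admission is classed as unrelated.

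**Row 4.** The rules contradict each other: the event meets both definitions and is also excluded. Because a serious event is defined as a kind of adverse event or reaction, losing adverse-event status also takes it out of the 48-hour notification to the sponsor and the monitoring committee.

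**Order of recording and causality.** The same section handles early pregnancy complications the other way round. They are recorded as adverse or serious adverse events, and only then held not to be reactions, because a causal link is thought unlikely. The third exclusion reverses that order.

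**Who judges.** The section does not say who decides that a hospitalisation is unrelated. Clinicians and trial staff know the arm, and no blinded assessor is named. Judgement by people who know the allocation is a fair inference, not a stated fact.

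**Contact.** The intervention arm has monthly calls and an in-person visit at week 13 (the schedule sections for weeks 2–12, 13 and 14–25). The Control section plans no adherence follow-up and a review after 6 months. Both arms may attend for ovulation induction from month 3, which narrows the gap in the second half without closing it.

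**Size of the recording risk, on assumed inputs.** Let r be the true rate of injuries leading to admission, equal in both arms. Let a and b be the shares dropped as unrelated in the intervention and control arms. With 600 per arm (Sample size calculation):

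- expected recorded events: 600 × r × (1 − a) against 600 × r × (1 − b)
- apparent risk ratio: (1 − a)/(1 − b), which does not depend on r

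With r assumed to be 2%, 600 × 0.02 = 12 true events per arm:

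| a | b | Recorded, intervention v control | Apparent risk ratio |
|---|---|---|---|
| 0 | 0 | 12 v 12 | 1.0 |
| 0.5 | 0.5 | 6 v 6 | 1.0 |
| 0 | 0.25 | 12 v 9 | 1.33 |
| 0 | 0.5 | 12 v 6 | 2.0 |
| 0.25 | 0 | 9 v 12 | 0.75 |
| 0.5 | 0 | 6 v 12 | 0.5 |

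Applied equally, the exclusion loses events but leaves the ratio intact. It distorts the ratio only when applied differently by arm, and then in either direction. The values of r, a and b are illustrations. Nothing in the documents fixes them.

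**The case against.** The strongest defence is that the notable-event flag is an addition and does not replace ordinary recording. The general definitions name no arm, so a control-arm fracture is still an adverse event, and a serious one if it needs admission or medical intervention. The third exclusion is worded alike for both arms, and its examples are incidental illness, not injury. The trial management group reviews adverse events, and the monitoring committee is treatment-blind apart from the statistician. Closer watching of the tested programme for plausible harms is a legitimate monitoring choice. The primary outcome, sample size and efficacy analysis are untouched.

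Most of this stands, and it limits the point. A reader might infer that the whole safety comparison is biased by definition, or that a table of notable events with an empty control column would produce a spurious significant difference. The documents support neither. Asymmetry by definition is confined to the notable-event category, the plan states no test on that category, and any event rate would have to be assumed. A reader might also take the food-allergy rule as restricted to the intervention arm, but its sentence does not say so.

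The defence does not remove the two defects. Targeted monitoring does not explain a one-sided injury category when both arms receive exercise advice. Blinded committee review cannot recover events that were never recorded. Condensing a full protocol into an article may explain missing detail, but this contradiction lies between rules that the article states.

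**Conclusion.** The point holds for the two stated rules and no further.

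- **Notable events.** The category exists in one arm only, so its counts are not comparable between arms. This follows from the text and needs no assumption.
- **Unrelated hospitalisations.** The exclusion contradicts the section's definitions of adverse and serious adverse events, and places causality before recording. This too follows from the text. That it would be applied differently by arm is a risk. It rests on the inference that people who know the allocation make the judgement, and its direction and size are unknown.

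Unequal contact between arms adds to the risk of unequal recording. The omission of death from the listed SAE criteria is a minor wording point with no bearing on comparability. The correction is worth making because the rules, followed exactly, yield non-comparable injury flags and can leave serious events out of the monitoring committee's data.

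**What to change.** 1. Word the injury rule for both arms, and state that the food-allergy rule covers both.
2. Delete the third exclusion, or reconcile it with the adverse-event definition, so that every hospitalisation for an untoward event is recorded as an adverse or serious adverse event in both arms.
3. Record relatedness as a separate field, completed after the event is entered.
4. When adverse-event counts are interpreted, state that the arms had different contact schedules. Rewording the safety section does not remove that difference.
5. As a minor edit, name death among the SAE criteria.

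The cost is wording in the safety section, small changes to the case report form, and a few more event entries. Sample size and the efficacy analysis do not change.

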### Data collection and management

The data related to clinical characteristics, anthropometric measurements and endocrinological parameters of the participants at the baseline will be collected. Subsequent information collected at the follow-up along with outcome data will be captured at the end of the treatment period. The data will be collected from the source data and entered into the central database by the data operator. Each entry will be double-checked by one of the trial staff. Finally, as a quality control measure, 10% of the entries will be validated by the central monitoring team who will cross-verify the entries by comparing the CRF/source data, if deemed necessary. The CRFs provided to the central monitoring team will carry only anonymised participant-related data. The data access will be restricted to designated trial staff at each site and the members of the sponsoring agency, ICMR to maintain data confidentiality.

### Data monitoring

The central data monitoring committee will be set up and meet before the trial starts recruitment. The group will have access to confidential information as well as accumulating data including SAEs. The data monitoring committee (DMC) will review the trial data routinely and using statistical analysis, inform the trial steering committee about the following: (i) unequivocal evidence that one arm is doing poorly compared to the other arm as mentioned under stop trial conditions, (ii) good evidence that one arm better than the other as mentioned under stop trial conditions, (iii) any protocol changes and (iv) safety data review. However, we do not anticipate any major safety concerns due to the nature of the intervention.

The DMC will consist of trial statistician as well as independent members who are not part of the trial and submit periodic reports to the trial steering committee (TSC). All the members will be treatment blind except the statistician. They will also conduct the interim analysis at 30 months.

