### Trial oversight

We will constitute a trial managing group (TMG) consisting of PIs/co-PIs and trial managers from all the sites, the trial statistician and representatives from the sponsor. The TMG will meet at prespecified intervals for reviewing and coordinating the conduct of the trial at the site level. The TSC will also be formed for the trial governance. The TSC will have members from the TMG (PIs and trial statistician), independent members and Patient and Public Involvement (PPI) representative. The main role of TSC will be to provide overall supervision for the trial and give advice through its independent chair on trial-related matters. The final decision regarding the continuation of the trial will rest with the TSC. The TSC will also oversee the dissemination of the results of the trial and the publication process.

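### The only DMC member with unblinded access, the trial statistician, also sits on the trial managing group and on the steering committee that decides continuation

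*Protocol article*

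**What the plan says.** Two adjoining sections of the protocol article assign the roles.

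**Data monitoring.** On composition: "The DMC will consist of trial statistician as well as independent members who are not part of the trial". On blinding: "All the members will be treatment blind except the statistician". On access: "The group will have access to confidential information as well as accumulating data including SAEs". The committee reviews the data routinely and, on formal analysis, "They will also conduct the interim analysis at 30 months". Among the matters it reports to the TSC is "good evidence that one arm better than the other as mentioned under stop trial conditions".

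**Trial oversight.** The TMG is described as "consisting of PIs/co-PIs and trial managers from all the sites, the trial statistician and representatives from the sponsor", and it coordinates conduct at the sites. For the steering committee: "The TSC will have members from the TMG (PIs and trial statistician), independent members", plus a patient and public representative, with advice given through an independent chair. On authority: "The final decision regarding the continuation of the trial will rest with the TSC".

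**The concern.** Comparative interim results are normally confined to people who neither run the trial nor decide its future on behalf of those who run it. Someone who knows how live birth is trending by arm can affect decisions on continuation, protocol changes or analysis without intending to.

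Here the one DMC member with access to unmasked results belongs to both other bodies. Those bodies are active. Under Recruitment strategies, the TMG meets monthly and presses slow sites, and recruitment may be moved between sites after a one-year review. Under Data monitoring, protocol changes are among the matters the DMC raises with the TSC, so the same person would advise on a change in one committee and receive that advice in another. Care is open-label, and the Blinding section concedes that performance bias cannot be excluded. At stake is mainly the credibility of the final comparison: a critic could ask whether any mid-trial decision was made with knowledge of the results.

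**Working it through.** No figure in the plan bears on this point. The sample size calculation is unaffected. The check sets the two sections side by side.

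| Role | DMC | TMG | TSC |
|---|---|---|---|
| Trial statistician | yes, not blind | yes | yes |
| Site principal investigators | no | yes | yes |
| Sponsor representatives | not listed | yes | not listed |
| Independent DMC members | yes, treatment blind | not listed | not listed |

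1. **Is it the same person?** Both sections use the term trial statistician. The blinding sentence says only the statistician, but the DMC composition names just one, so it can only mean the trial statistician. The composition sentence itself sets that role apart from the independent members.
2. **What can that person see?** The DMC has access to accumulating data, reviews it routinely with statistical analysis and conducts the 30-month interim analysis. Its one unblinded member therefore has access to results by true arm at the interim analysis, and possibly earlier through routine review.
3. **Where else does that person sit?** On the TMG with investigators from every site, and on the TSC, which makes the final decision on continuation.
4. **Is there a separation?** Neither section names a second statistician, a recusal or a limit on TMG and TSC attendance. The report to the TSC covers evidence between arms and is not confined to a recommendation.
5. **Does the open-label design answer this?** No. A clinician who knows each patient's allocation still does not know the pooled live birth comparison across five sites. That pooled comparison is what interim confidentiality protects.

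The overlap therefore follows from what the article states, and not merely from something it omits.

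**The case against.** The strongest reply has five parts.

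- **No disclosure is planned.** A reader might infer that interim results will reach the investigators. No sentence says so. What is shown is access without separation. This part stands.
- **Blind may mean masked labels.** A reader might infer that the roles are reversed, with the independent members seeing no comparison and the non-independent member seeing all of it. The section gives the whole committee access to accumulating data and expects it to judge one arm against the other, so review by coded arm is a natural reading. Masked review is a debatable choice, but a legitimate one. This part also stands.
- **A charter may hold the firewall.** The section refers to stopping conditions that the article does not reproduce, so fuller rules probably exist, and closed sessions and report content commonly sit there. Their absence here is no fault in itself. But a charter that named a different unblinded statistician would contradict the article, so the wording needs changing either way.
- **Safeguards exist.** The TSC has an independent chair, independent members and a public representative, and one statistician does not decide alone. This softens the problem, but the knowledge is still in the room.
- **The route to bias is indirect.** Live birth is objective, allocation is concealed until randomization, and letrozole is limited to three cycles. True, so the risk lies more in decisions about conduct and continuation than in outcome assessment.

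**Conclusion.** The point holds as an overlap of roles: the unblinded DMC member is also a member of the body that runs the trial and of the body that decides whether it continues. It rests on reading trial statistician as one role throughout, which the wording supports.

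Its size cannot be given. A reader might try to measure it by counting the women still to be recruited after the interim analysis. That count would need an assumed accrual pattern and a start for the 30-month clock, which the article does not state. It would also miss any access through earlier routine review, and it would measure exposure, not bias.

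This is a governance weakness that should be corrected because correction is cheap. It is not evidence that the trial's results will be biased.

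**What to change.** Amend Data monitoring and Trial oversight together so that whoever is unblinded on the DMC serves on neither the TMG nor the TSC until database lock. Either arrangement would do:

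- the trial statistician stays on the DMC and steps off the TMG and TSC until lock; or
- one of the independent DMC places already planned is held by a statistician who prepares the by-arm report, while the trial statistician stays on the TMG and TSC, blind to comparative data.

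In either case, state that the DMC passes the TSC a recommendation and not comparative results.

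The cost is committee wording and a matching charter entry. Sample size, treatment and analysis do not change. The first arrangement needs no added post, but the TMG and TSC lose that statistician's input until lock. The second means that the trial statistician cannot brief the DMC by arm. It also assumes that an independent place can go to a statistician, since the article gives neither the number nor the expertise of those members.

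The change does not touch the data access that Data collection and management grants to site staff and the sponsor. The sponsor should confirm separately that this access does not yield pooled results by arm.
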